## **12.2 Descriptive analysis**

The statistical analysis will first present a descriptive analysis of the study population and their measured parameters with absolute and relative frequencies (and their 95% confidence intervals) for the categorical variables, and evaluation of means and distributions, medians and inter quartiles for the quantitative variables.

As the CONSORT guidelines recommend, the principal characteristics of the patients will be compared between the two groups at inclusion, but no statistical analysis of this will be performed. The comparability of the two arms will be assessed clinically rather than statistically. A flow chart showing the number of eligible patients, the number of patients included, and the number of patients randomized will be presented. The characteristics of patients lost to follow up over the course of the study will be described.

## **12.3 Outcomes analyses**

### **12.3.1 Analysis of the primary objective:**

The primary objective of this study is to compare the clinical remission rate over one year between patients with and without personalized treatment.

The clinical remission rate at M12 will be compared between the groups using a Chi-square test or Fisher's exact test in case of small sample.

If necessary, a multivariate logistic regression analysis will be performed to assess the relationship between the clinical remission and the treatment group, adjusted for the potential confounding factors.

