## 1.2 Epitope Spreading as prognosis biomarker

Our first objective is to better select patients who will benefit from immunosuppressive treatment. Although the identification of PLA2R1-Ab has been paradigm shifting in the diagnosis and management of patients, there are outliers who call for additional biomarkers. Indeed, antibodies may persist during apparent clinical remission and conversely a drop in antibody titer may not be associated with a clinical remission (14, 19, 20).

PLA2R1 is a 180-kDa membrane receptor with a large extracellular region comprising 10 distinct globular domains including a cysteine-rich domain (CysR), a fibronectin type II domain (FNII), and 8 distinct C-type lectin domains (CTLD1-8) (21). Each domain is separated by a small linker sequence of about 10 amino acids. An immunodominant epitope was first identified in a region spanning the CysR-FNII-CTLD1 domains (22), which was further restricted to the CysR domain alone (23). In a first study, we identified reactive epitopes in the CysR, CTLD1 and CTLD7 domains, and that all samples reacted with CysR domain confirming that CysR was the immunodominant epitope. We further showed that patients with anti-CysR-restricted activity were younger, had lower proteinuria, and exhibited a higher rate of spontaneous remission and lower rates of renal failure progression (24). Conversely, high PLA2R1-Ab activity and epitope spreading beyond the CysR epitope were

independent risk factors of poor renal prognosis in a collection of 69 sera from five French nephrology centers.

In a second prospective trial we analyzed the predictive value of epitope-specific PLA2R1-Ab titer and epitope spreading at diagnosis in the 58 PLA2R1-Ab positive patients from GEMRITUX randomly allocated to rituximab plus NIAT (n=29) or NIAT (n=29). In adjusted analysis, epitope spreading at baseline was associated with a decreased remission rate at month 6 (OR, 0.16; 95% CI, 0.035 to 0.72;  $p=0.0171$ ) and last follow-up (median, 23 months; OR, 0.14; 95% CI, 0.03 to 0.64;  $p=0.0107$ ), independently from age, gender, baseline PLA2R1-Ab level and treatment group (Seitz-Polski et al. JASN Accepted august 2017).

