## 7. Sample size calculation

### 7.1 Estimate of remission rate in the personalized arm

According to our preliminary data, about 30% of patient with iMN have CysR restricted activity at diagnosis. About 50% will enter in spontaneous remission after 6 months of NIAT and 40% after NIAT + Rituximab at low doses (375 mg/m^2 D0 and D7).

About 70% of patients have CTLD1/7 activity, in our cohorts, about 85% entered in remission after repeated pulses of high doses of rituximab.

We therefore expect a remission rate of 80% at M12 in the personalized arm.

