### **8.3 Inclusion and randomization = M0**

After signing the study consent, participants will be randomized in one of the two treatment arms:

- GEMRITUX treatment
- Personalized treatment

Randomization will be balanced (1:1). Centralized block randomization will be conducted by the *Département de la Recherche Clinique et de l'Innovation* (DRCI) (Department of Clinical Research and Innovation) at CHU Nice (Nice University Hospital). Taking into account the size of our study

sample which is relatively small and the high number of participating centers, (which is high in light of the need to ensure that the intended level of recruitment is met), it does not seem appropriate to account for the center as a stratification parameter.

Randomization will be integrated in the electronic case report file (e-CRF) devised specifically for the study with Redcap® software. Using their personal access details to login, the investigator will provide the necessary patient information (i.e. the first letter of their first and last name and their month and year of birth) for random allocation to treatment by the online randomization module (Redcap®). Randomization can then take place around the clock. The treatment group and inclusion number for the patient will then be relayed to the investigator and the central lab team. The patient's trial records will then be created automatically, allowing data to be entered.

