### 8.5 Definition of patient data to be gathered and directly entered in the patient electronic case file, which will be considered the source data:

#### Inclusion/Randomization visit (M0)

- Consultation date
- Demographic data: date of birth, sex
- History of MN
- Paraclinic tests to eliminate secondary MN when performed: body scan, anti-nuclear antibodies, HBV, HCV serologies
- Current treatment
- Clinical examination: weight, height, blood pressure, edema
- Blood sample: urea, creatinine, electrolytes (Na, K, Cl, HCO3), protein, albumin, full blood count
- Urine collection on a spot morning sample: protein, albumin, urea, creatinine
- Centralized assays : for both groups,

- 2 dry tubes of 5 ml of blood and 2 EDTA tubes of 3 ml of blood will be shipped to Nice at room temperature for PLA2R1-Ab, epitope profile determination, anti-rituximab antibodies, B and T cells counts (see manual lab),
  - 1 lithium heparin tube of 4 ml of blood for cytokine profile analysis will be shipped to Nice at 4°C.
- 
- Start vaccination (pneumococcal and influenza vaccine) between randomization and first injection at the latest.
  - In the GEMRITUX arm, plan M3 in 3 months +/-15days and hand out a prescription to the patient for blood and urine analyses\* (results needed for the next visit as per routine follow-up);
  - In the Personalized Treatment arm, plan next visit according to the epitope profile results provided by the central lab within 48 hours:
    - Restricted anti-CysR activity: 6-month symptomatic treatment as in GEMRITUX arm - > plan M3 visit in 3 months +/-15 days and hand out a prescription to the patient for blood and urine analyses\* (results needed for the next visit as per routine follow-up);
    - Anti-CTLD1/7 activity: plan two 1g rituximab infusions at 2-week interval +/-2 days. The treatment should start between 5 and 14 days after randomization. After the first injection, plan M3 visit in 3 months +/-15 days and hand out a prescription to the patient for blood and urine analyses\* (results needed for the next visit as per routine follow-up)

\* Blood sample: urea, creatinine, electrolytes (sodium, potassium, chloride, bicarbonate), protein, albumin, full blood count.

Spot morning urine sample: protein, albumin, urea, creatinine.

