### **12.3.2 Analysis of the main secondary objective:**

The secondary objectives consist in comparing several parameters between both treatment groups (GEMRITUX versus Personalized treatment) at different study timepoints according to each specific objective. The secondary assessment criteria can be grouped into two categories:

- Objectives 1, 2 and 3: binary criteria (remission clinical or immunological), compared at different timepoints between the two groups. Comparisons will be performed using a Chi-square test or Fisher's exact test in case of small sample.
- Objectives 4, 6 and 8: quantitative criteria compared at different timepoints between the two groups. Comparisons will be performed using a student t-test (or mann-whitney rank sum test in case of non-parametric variables).
- Objectives 5, 7: Quantitative criteria evolution (changes from baseline), defined as the difference between the  $M_x$  and  $D_0$  values,  $\Delta\text{variable} = \text{Variable } M_x - \text{Variable } D_0$ . Analyses will use an analysis of covariance which takes into account the initial values as a covariate. The dependent variable will be the  $\Delta\text{variable}$  and the variable of interest the treatment group.
- Objective 9: Severe infections will be described by type and their frequencies, absolute and relative, presented. The rate of patients presenting with at least one severe infection during follow-up will be compared between the two groups using a Chi-square test or Fisher's exact test in case of small sample.

Further multivariate analyses will be eventually discussed in case of imbalanced potential confounding factors between the groups.

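### Neither the randomization nor the primary test uses the M0 epitope profile, the strongest baseline predictor the protocol cites, and covariate adjustment is left conditional

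*Protocol*

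**What the plan says.** Section 8.3 sets the allocation: "Randomization will be balanced (1:1). Centralized block randomization will be conducted by the" sponsor's research department. Center is the only stratification factor discussed, and it is rejected: "it does not seem appropriate to account for the center as a stratification parameter". The epitope profile is not considered.

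Section 12.3.1 fixes the primary test: "The clinical remission rate at M12 will be compared between the groups using a Chi-square test or Fisher's exact test in case of small sample". It then adds: "If necessary, a multivariate logistic regression analysis will be performed to assess the relationship between the clinical remission and the treatment group", adjusted for confounders that are not named and with no stated trigger. For the secondary outcomes, Section 12.3.2 ties adjustment to observed imbalance: "Further multivariate analyses will be eventually discussed in case of imbalanced potential confounding factors between the groups".

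On the marker, Section 1.2 reports: "In adjusted analysis, epitope spreading at baseline was associated with a decreased remission rate at month 6", with an odds ratio of 0.16 (95% CI 0.035 to 0.72), independently of age, gender, antibody level and treatment group. At last follow-up the odds ratio was 0.14. Section 7.1 expects that "about 30% of patient with iMN have CysR restricted activity at diagnosis" and that about 70% have CTLD1/7 activity.

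Section 8.5 has M0 blood assayed centrally in both groups. In the personalized arm the site is told to "plan next visit according to the epitope profile results provided by the central lab within 48 hours".

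**The concern.** The profile that defines the personalized strategy is also a strong baseline predictor of the outcome. Under Section 8.5, a patient who is CysR-restricted at M0 is managed in the personalized arm as in the control arm up to M6. If still restricted with active disease at M6, that patient then receives the control regimen. The arms therefore differ almost entirely in patients with anti-CTLD1/7 activity, and the CysR-restricted share acts mainly as prognostic background.

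In a trial of 64 patients with no stratum, that background can be unequal by chance, and an unadjusted test does nothing about it. The conditional clause also leaves room for judgement: in an open-label trial where Section 12.2 has comparability of the arms assessed clinically, nothing fixes when an adjusted model is run, on which factors, or with what standing. At stake are the precision of the one primary estimate and the certainty that there is only one primary p-value.

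**Working it through.** **Inputs.** CysR share 30%, CTLD1/7 share 70%, personalized-arm rate 80% (Section 7.1); control rate 45%, 29 analysed per group, 64 in total, so 32 per arm (Section 7.2); 5% threshold (Section 12.1).

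**The plan's own figure.** With two-sided alpha 0.05, power 0.80 and pooled variance, n = [1.96·√(2·0.625·0.375) + 0.8416·√(0.45·0.55 + 0.80·0.20)]² / 0.35² = (1.342 + 0.537)² / 0.1225 = 28.8, so 29. This treats the printed alpha and beta as transposed, which is a separate matter.

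**Stratum rates (assumption).** The protocol gives no control-arm M12 rate by epitope. I set the CysR rate c equal in both arms and kept the margins at 45% and 80%. CTLD1/7 rates are then (0.45 − 0.3c)/0.7 in control and (0.80 − 0.3c)/0.7 in the personalized arm. Section 7.1 can be read as c = 0.50 + 0.40 × 0.50 = 0.70, which fits its total: 0.3 × 0.70 + 0.7 × 0.85 = 0.805. Read additively it gives 0.50 + 0.40 = 0.90. I show 0.60 to 0.90.

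**Chance imbalance.** Take two independent Binomial(32, 0.30) counts. The probability of a gap of 4 or more is 0.339, and of 5 or more 0.219. The mean absolute gap is 2.9 patients.

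**Shift from a 5-patient gap.** At control-arm rates in both arms (no treatment effect), shift = (5/32) × (c − control CTLD1/7 rate):
- c = 0.70: 0.156 × (0.700 − 0.343) = 5.6 points
- c = 0.90: 0.156 × (0.900 − 0.257) = 10.0 points

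Under the planned effect the shift is smaller, because personalized CTLD1/7 patients also do well. Splitting the gap evenly between the arms gives (2.5/32) × [(c − control CTLD1/7 rate) + (c − personalized CTLD1/7 rate)]:
- c = 0.70: 0.078 × (0.357 − 0.143) = 1.7 points
- c = 0.90: 0.078 × (0.643 + 0.143) = 6.1 points

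**Power and type I error.** Simulation with 400,000 trials per setting, 29 per arm, unstratified allocation; CMH is the Cochran-Mantel-Haenszel test stratified by epitope profile:

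| CysR rate c | Control / personalized CTLD1/7 rate | Power, crude chi-square | Power, CMH | Type I error if either result counts |
|---|---|---|---|---|
| 0.60 | 0.386 / 0.886 | 79.6% | 80.6% | 5.7% |
| 0.70 | 0.343 / 0.843 | 79.5% | 80.7% | 6.2% |
| 0.80 | 0.300 / 0.800 | 79.6% | 82.8% | 6.8% |
| 0.90 | 0.257 / 0.757 | 79.6% | 86.3% | about 7.4% |

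Under the null at 29 per arm, the crude chi-square rejects about 4.7% of the time and CMH 4.9 to 5.0%. At 32 per arm crude power is about 85%, and CMH gives 84.7%, 84.9%, 86.4% and 89.4%. At that size the gain appears only at the higher CysR rates.

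**The case against.** The strongest reply is that a primary test is fixed. Section 12.3.1 states the chi-square or Fisher comparison outright, and the logistic model is a further, conditional analysis. A reader might infer that the sponsor will choose between crude and adjusted results after seeing the data. The protocol does not say that, so the 5.7 to 7.4% describes a use the wording leaves open, not a planned one. The covariate list and trigger may also sit in a SAP that is not shown. That stands for the list. It does not answer the unstratified blocks or the unadjusted primary test, which the protocol itself fixes.

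Other stronger readings also go too far:
- **That the planned test is invalid.** Averaged over randomizations it is not, and its confidence interval already carries the imbalance.
- **That a serious imbalance is likely.** A gap of 4 or more has about a one-in-three chance, and the typical gap is about 3 patients.
- **That the whole 35-point effect comes from CTLD1/7 patients.** A patient CysR-restricted at M0 who shows CTLD1/7 activity with active disease at M6 gets a different regimen from control.
- **That including CysR patients dilutes the trial.** The objective compares two strategies in all eligible patients, and the 80% is built on the 30/70 mix.
- **That spreading is the strongest predictor of any kind.** Section 1.3 cites a hazard ratio of 7.90 for antibody depletion after rituximab. That is post-treatment and cannot be a stratum, so the claim holds for baseline predictors only. The 0.16 comes from 58 patients and has a wide interval.

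**Conclusion.** The point holds as a recommended improvement, not as a flaw that invalidates the trial. The plan omits from both allocation and primary analysis a baseline factor that it measures centrally in every patient and itself reports as strongly prognostic, and it leaves adjustment without a rule.

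The size is modest. There is a 22% chance of a gap of 5 or more patients. Such a gap is worth 5.6 to 10 points at control-arm rates for CysR remission of 70 to 90%, and less under the planned effect. The power gain at 29 per arm is about 1 to 7 points, and close to nothing at 32 per arm if the CysR rate is 60 to 70%. The main return is protection against chance imbalance and a single fixed primary result. All stratum-specific figures rest on the assumption of equal CysR rates in both arms and on margins of 45% and 80%.

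**What to change.** In Section 12.3.1, make the primary test a Cochran-Mantel-Haenszel test stratified by the central M0 epitope profile (CysR-restricted versus CTLD1/7), reported with a stratified risk difference and 95% CI. Delete the condition that opens the logistic regression sentence, and label any further adjusted model a sensitivity analysis.

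If accrual has not begun, also stratify the blocks in Section 8.3 by the same factor. Randomization would then wait up to 48 hours for the result. The Summary already ships samples before randomizing, and Section 6.2 makes central antibody confirmation an eligibility matter, so the added delay is small; Section 8.3, which randomizes after consent, would need to match.

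If accrual has begun, the stratified analysis can still be adopted, because M0 profiles are assayed in both arms. It is not free: it needs a protocol amendment and, if that counts as a substantial modification, the ethics opinion and agency authorization described in Section 16.4. Neither route needs extra patients or assays.

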### **12.3.2 Analysis of the main secondary objective:**

The secondary objectives consist in comparing several parameters between both treatment groups (GEMRITUX versus Personalized treatment) at different study timepoints according to each specific objective. The secondary assessment criteria can be grouped into two categories:

- Objectives 1, 2 and 3: binary criteria (remission clinical or immunological), compared at different timepoints between the two groups. Comparisons will be performed using a Chi-square test or Fisher's exact test in case of small sample.
- Objectives 4, 6 and 8: quantitative criteria compared at different timepoints between the two groups. Comparisons will be performed using a student t-test (or mann-whitney rank sum test in case of non-parametric variables).
- Objectives 5, 7: Quantitative criteria evolution (changes from baseline), defined as the difference between the  $M_x$  and  $D_0$  values,  $\Delta\text{variable} = \text{Variable } M_x - \text{Variable } D_0$ . Analyses will use an analysis of covariance which takes into account the initial values as a covariate. The dependent variable will be the  $\Delta\text{variable}$  and the variable of interest the treatment group.
- Objective 9: Severe infections will be described by type and their frequencies, absolute and relative, presented. The rate of patients presenting with at least one severe infection during follow-up will be compared between the two groups using a Chi-square test or Fisher's exact test in case of small sample.

Further multivariate analyses will be eventually discussed in case of imbalanced potential confounding factors between the groups.

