## 2.2 Secondary Objectives

The following objectives are to compare between a personalized treatment of iMN driven by anti-PLA2R1 antibody epitope profiles and the GEMRITUX therapeutic protocol:

1. Complete clinical remissions at M6, M9, M12, M18, M24
2. Partial clinical remission at M6, M9, M12, M18, M24
3. Immunological remissions at M6, M9, M12, M18, M24
4. Proteinuria and albuminuria at M6, M9, M12, M18, M24
5. Changes in proteinuria and albuminuria from baseline at M6, M9, M12, M18, M24
6. Serum creatinine and estimated glomerular filtration rate (eGFR) at M6, M9, M12, M18
7. Changes in serum creatinine and eGFR from baseline at M6, M9, M12 and M18
8. PLA2R1-Ab titers at M6, M9, M12, M18 and M24
9. Recording all AEs/SAEs during study follow-up, 24 months

The following objectives aim to study risk factors for remission or relapse:

10. To determine risk factors for remission (immunological and clinical, partial or complete) at M12 in patients pooled from the two arms
11. To determine risk factors for relapse (between M12 and M24) in patient responders at M12, pooled from the two arms

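### Objective 8: PLA2R1-Ab titre is compared only without its M0 value, so the test is valid but gives up precision that the plan already takes for the other continuous outcomes

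*Protocol*

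**What the plan says.** Protocol section 12.3.2 sorts the continuous secondary outcomes into two groups.

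- **Follow-up values.** "Objectives 4, 6 and 8: quantitative criteria compared at different timepoints between the two groups". The method is: "Comparisons will be performed using a student t-test", or "mann-whitney rank sum test in case of non-parametric variables". No covariate is mentioned.
- **Changes from baseline (objectives 5 and 7).** "Analyses will use an analysis of covariance which takes into account the initial values as a covariate".

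Section 2.2 shows which variables fall where. Objective 5 is "Changes in proteinuria and albuminuria from baseline at M6, M9, M12, M18, M24" and objective 7 is "Changes in serum creatinine and eGFR from baseline at M6, M9, M12 and M18". These are the change counterparts of objectives 4 and 6. Objective 8 is "PLA2R1-Ab titers at M6, M9, M12, M18 and M24" and has no such counterpart.

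The M0 titre is available. Section 8.5 and the schedule of assessments have PLA2R1-Ab measured centrally at M0 in both arms. The last sentence of section 12.3.2 leaves open further multivariate analyses if confounders prove imbalanced, but it names no covariate and no endpoint.

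**The concern.** Section 1.1 says that a high titre at presentation, and its persistence, predict poor outcome, and it treats lowering the titre as a goal of therapy. Yet titre is the only continuous efficacy outcome with no committed baseline-adjusted comparison, and the protocol gives no reason for the difference.

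Section 8.3 describes block randomisation without stratification by centre and names no other stratification factor, so nothing in the design balances baseline titre. In a trial of 64 patients with a rare disease, a covariate that is already collected can narrow the confidence interval at no extra burden to patients. The protocol names the test, so this is a choice it has made and not a detail left to the SAP.

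**Working it through.** **Inputs from the protocol.** Total 64 patients (section 7.2), allocated 1:1 (section 8.3), so 64/2 = 32 per arm. Tests are at 5% (section 12.1), taken here as two-sided. The protocol states no power, SD or baseline-to-follow-up correlation for objective 8, so there is no figure of its own to reproduce.

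**Assumptions.** ρ is the within-arm correlation of M0 titre with follow-up titre on the analysis scale; 0.2, 0.5 and 0.7 are shown. For power, the assumed titre ratio is 0.55 and the SD of log titre 1.0. All 64 patients contribute.

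**Step 1: precision.** With the baseline as covariate, the variance of the treatment difference is multiplied by about 1 − ρ² and the standard error by √(1 − ρ²). The unadjusted sample size giving the same precision is 32/(1 − ρ²) per arm. The difference detectable with 80% power is (1.96 + 0.84) × √(2/32) = 0.70 SD unadjusted, and that figure times √(1 − ρ²) adjusted.

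| ρ | Variance factor | SE factor | Fall in SE | Equivalent unadjusted n per arm | Detectable difference |
|---|---|---|---|---|---|
| 0 | 1.00 | 1.00 | none | 32 | 0.70 SD |
| 0.2 | 0.96 | 0.98 | 2% | 33 | 0.69 SD |
| 0.5 | 0.75 | 0.87 | 13% | 43 | 0.61 SD |
| 0.7 | 0.51 | 0.71 | 29% | 63 | 0.50 SD |

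The fall in SE does not depend on the number per arm, so losses to follow-up do not change it.

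**Step 2: power, no assay floor.** The log difference is −ln 0.55 = 0.598. Approximate power is Φ(0.598 / [0.25 × √(1 − ρ²)] − 1.96), where 0.25 = √(2/32).

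- Unadjusted log t-test: Φ(2.39 − 1.96) = 67%.
- ANCOVA, ρ = 0.2: Φ(2.44 − 1.96) = 68%.
- ANCOVA, ρ = 0.5: Φ(2.76 − 1.96) = 79%.
- ANCOVA, ρ = 0.7: Φ(3.35 − 1.96) = 92%.

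Simulation under the same assumptions gives slightly lower values: about 66%, 78% and 90% for log ANCOVA, and 62 to 65% for Mann-Whitney whatever ρ is. Mann-Whitney is the fair comparator, because the protocol sends skewed variables to it.

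**Step 3: assay floor.** With about 31% of control and 54% of personalized values at the floor, simulated power for Mann-Whitney against log ANCOVA is 57% against 64% at ρ = 0.5 and 56% against 74% at ρ = 0.7, with no gain at 0.2 to 0.3. With half of control titres at the floor and the limit itself substituted, Mann-Whitney has 51%, and log ANCOVA 47% at ρ = 0.2 and 53% at 0.5. Substituting half the limit raises the last figure to 59%, so the constant must be fixed in advance. A rank-based ANCOVA stays at or above Mann-Whitney in this setting.

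**Step 4: objectives 4 and 6.** Let Y₀ be baseline, Y₁ follow-up and G the treatment group. The model Y₁ − Y₀ = a + τG + βY₀ is the same as Y₁ = a + τG + (β + 1)Y₀. The treatment effect τ, its standard error and its p-value are identical. The ANCOVA for objectives 5 and 7 therefore already supplies the adjusted comparison of follow-up values, provided that change is the absolute difference defined in section 12.3.2. Section 3 defines these changes as percentages, for which the identity fails, so the two definitions should be reconciled.

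**The case against.** Most of the case on the other side stands, and it limits the point.

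- **Validity.** A reader might infer that chance imbalance in baseline titre biases the comparison. It does not. Randomisation keeps the unadjusted test unbiased, and its standard error already reflects chance imbalance. Only efficiency is lost.
- **Objectives 4 and 6.** A reader might extend the criticism to proteinuria, albuminuria, creatinine and eGFR, which share the same unadjusted rule. Objectives 5 and 7 already adjust these variables (step 4). What remains is that two analyses of one variable could disagree and the protocol does not say which leads.
- **Size.** A simulated contrast of 47% power for a t-test on raw titres with 77% for log-scale ANCOVA at ρ = 0.5 overstates the gain. It changes the scale and the adjustment together. Against an unadjusted log t-test at about 66%, the covariate adds about 12 points at ρ = 0.5 and almost nothing at ρ = 0.2.
- **Other analyses of antibody response.** Objective 3 tests immunological remission (titre below 14 RU/ml, section 3) at the same visits, so the antibody goal is not neglected. That test is binary and also unadjusted, so it does not recover the precision.
- **Later adjustment.** The closing sentence of section 12.3.2 leaves room for it, but it depends on observed imbalance and commits to no covariate.
- **Choice between t-test and Mann-Whitney.** Checking test conditions first is routine (section 12.1) and is not a fault on which this point relies.

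**Conclusion.** The point holds for objective 8 alone, as a free improvement. The planned test is valid, but it leaves out a covariate that is already collected and that the plan uses for every other continuous efficacy variable.

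The direction is secure for any material ρ; the size is not known from the protocol. On the assumed range the standard error falls by 2% to 29%. Without an assay floor, power rises from about 62 to 65% (Mann-Whitney) to about 66%, 78% and 90 to 92% at ρ = 0.2, 0.5 and 0.7. These power figures rest on an assumed ratio of 0.55 and SD(log) of 1.0 with 32 per arm. If treatment drives many titres to the floor, or ρ is low, the gain is small, and log ANCOVA can fall slightly below Mann-Whitney.

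Nothing here touches the primary endpoint.

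**What to change.** In section 12.3.2, take objective 8 out of the t-test or Mann-Whitney rule and state:

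- The main analysis at each visit is an ANCOVA of log titre, with treatment group and log M0 titre as terms.
- Titres below the assay limit take one substitution value, fixed in advance.
- If a large share of titres lies at the limit, with the share set in advance, a rank-based ANCOVA with the rank of the M0 titre as covariate is used instead.
- Mann-Whitney is kept as a sensitivity analysis.

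For objectives 4 and 6, add no test. State that the adjusted result from objectives 5 and 7 takes precedence, and align the definition of change between sections 3 and 12.3.2.

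The cost is a short text change and slightly more analysis work. No new sample, visit or patient is needed.
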